### Interventions

Aside from the prehabilitation strategies, all patients enrolled will receive conventional perioperative recommendations, including those based on preoperative anesthesia assessments, drug treatment recommendations for chronic diseases, and recommendations to quit smoking and practice abstinence. The patients will also be provided information on anesthesia and surgical processes, according to each individual’s needs.

We will encourage the patients in both groups to choose their preferred types of exercise and form individual-specific prehabilitation plans. A prehabilitation instruction brochure will be distributed to patients along with a daily self-evaluation prehabilitation journal, where they can record their adherence to the prehabilitation plans. Standardized short message interviews will be sent to patients twice a week in the manner chosen by the patients to optimize adherence and promote timely feedback. The patients will receive intraoperative and perioperative care according to standard practice in terms of surgical procedures, anesthesia and analgesia management, and nursing care.

The patients will be encouraged to reach out to our researchers if there are injuries or discomforts during the follow-up period. Since the intervention is based on moderate exercise and nutrition supplements, and exercise plan is individualized to consider participants’ capacity and preference, harm of the intervention is considered minimal. However, if patients experience injuries or discomforts due to the exercises or whey protein supplement, the intervention will be discontinued and we plan to offer appropriate medical and financial support. At any point in the study period, if patients request to stop or pause the intervention, the intervention will be discontinued.

#### Multimodal prehabilitation strategy features

For the multimodal group, we will implement the following prehabilitation strategy:A 30-min aerobic exercise session will be performed at least 3 times a week; it will be divided into a 5-min warm-up (including ankle extensor lifts and static quadriceps contraction) and a 25-min aerobic exercise in the form of jogging, power walking, or cycling, depending on the patients’ individual choice. We will encourage patients to tailor their exercise intensity to the Borg Rating of Perceived Exertion (RPE) Scale [16] shown in Table 1 and target heart rate (HR), increasing or decreasing the intensity according to the level of exertion throughout the prehabilitation period. We will recommend that patients achieve moderate to high levels of exertion, as indicated by 13–16 points on the Borg RPE Scale and a target HR of (220 – age − resting HR) × 70% + resting HR. The methods of using the Borg RPE Scale and target HR to adjust the exercise intensity will be explained at the baseline interview, and both methods will be illustrated in the brochure we give the patients. We will also provide each patient with a pulse oximeter (Jiangsu Yuyue Medical Equipment & Supply Co., Ltd., 20172201070) to help monitor HR. For patients who choose an outdoor activity as their aerobic exercise training method, we will stress the importance of safety and advise them to avoid exercising outdoors on days with poor air quality index values (> 100).Guided resistance exercises will be performed at least twice a week. At the baseline interview, a research staff qualified in performing physical therapy training and evaluations will initially evaluate the physical status of the patients and then explain and demonstrate the resistance exercises. We will provide each patient in the multimodal group with two pulling straps of different elasticities. Resistance training will be performed with either strap, depending on the patient’s individual strength limits. Most patients will start training with the less elastic strap and advance to the more elastic strap once they feel that training with the less elastic strap requires too little effort. We will assign 4 pre-set resistance postures for the training sessions, involving 4 major muscle groups (upper and lower limbs, chest, and core muscles). The complete resistance training session will include 3 sets of exercises with an interval of 2 min between each set. Each set will include 10–12 repetitions of the 4 resistance postures. At the end of each complete session, the patients will be asked to evaluate their perceived exertion by using the Borg RPE Scale. The target score will be 13–16. The number of repetitions performed within each set and the strap selection should be adjusted on an individual basis throughout the prehabilitation period according to the Borg RPE scores.Breathing exercises will be performed at least 3 times per day, with each session lasting more than 10 min. We will introduce three types of exercises: (1) guided effective coughing (sit up and lean slightly forward, inhale fully then cough out in a short and forceful manner while engaging the core muscles), (2) blowing up a small balloon in one breath and blowing it up slowly for more than 5 s, and (3) breathing training with the Tri-Ball Respiratory Exerciser (Leventon S.A., Barcelona, Spain) that we will distribute. All three types of breathing exercises will be demonstrated at the baseline interview and explained in the brochure. The patients will be allowed to choose to conduct one or more types of breathing exercises in one session.Regarding nutritional advice and whey protein supplementation, patients’ nutritional status and dietary habits will be evaluated at baseline by a research staff member trained in nutriology. Nutritional advice predetermined by our nutritionists will be given to modulate the patient’s eating habits, mainly aiming at reducing fat-rich diets and increasing high-quality protein uptake. Patients with malnutrition will be advised to increase their calorie uptake. We will also provide patients in the multimodal group with whey protein powder (Inerish; Sino-American Medical Institute Inc., San Diego, CA) as a protein supplement and advise them to take it daily (20 g/day for males and 15 g/day for females). If patients plan on performing exercises that day, we will advise that the whey protein powder is taken within 1 h postexercise, promoting muscle synthesis.Psychological therapy will include listening to soothing music, broadcasts, or other relaxing activities of the patients’ choice before sleep. We will provide each patient in the multimodal group with a simple music player with prerecorded relaxing, classical music tracks and encourage patients to use it if they prefer this type of relaxation method. We will also encourage patients to choose their preferred methods of relaxation, including listening to audiobooks, meditating, and watching relaxing television shows.

**Table 1 Tab1:** Borg RPE Scale

Score	Level of exertion
6	No exertion at all
7	Extremely light
8	Minimal recognition of effort
9	Very light (equivalent to walking at your own pace for several minutes)
10	Could just start to beware of breathing
11	Fairly light (conversation is easy and feel like you could keep the pace for a long time)
12	Light
13	Somewhat hard, but still feel able to continue
14	You could hear your breathing clearly but not struggling
15	Hard (you could talk but not in full sentences)
16	Heavy
17	Very hard (you could continue but would be pushing yourself to feel very fatigued)
18	You could not talk because of the heavy panting
19	Extremely hard
20	Maximal exertion

#### Aerobic prehabilitation strategy features

The aerobic group will receive the same instructions regarding the individualized home-based aerobic exercise program as the multimodal group will, but they will not receive advice regarding the other aspects of their behaviors. These patients will also be advised to record their daily exercises in a prehabilitation journal and will receive the same follow-up interviews twice a week.

### Outcomes

The primary outcome will be the perioperative 6MWD (baseline, 1 day presurgery, and 30 days postsurgery). The 6MWT will be conducted following the guidelines of the American Thoracic Society (ATS) [17]. The research staff members who will be involved in performing the 6MWT will all be trained before administering this test. We will conduct the 6MWT indoors in a 30-m-long corridor in PUMCH. We will ensure that supplies needed for safety issues are readily available whenever the 6MWT is performed, including oxygen, sublingual nitroglycerine, aspirin, and albuterol. All the staff members who will be involved have been previously certified in cardiopulmonary resuscitation. The 6MWT will be conducted in a standard manner. From the 10-min rest period before the test to all the verbal instructions provided to the patients before and during the test, all procedures will be performed in accordance with the standard ATS guidelines.

We will record the patients’ sex, age, height, weight, medications before the test, and whether they need oxygen supplementation during the test. We will measure blood pressure, HR, oxygen saturation, and the Borg RPE score before and after the test. We will note the number of laps and calculate the 6MWD.

The secondary outcomes will include the perioperative pulmonary function test results, including the FEV1, FEV1%, FVC, FVC%, FEV1/FVC, PEF, and PEF% values (baseline, 1 day presurgery, and 30 days postsurgery); the perioperative HADS and WHODAS 2.0 (baseline, 1 day presurgery, and 30 days postsurgery); post-surgery QoR-15 (3 consecutive days after surgery); prognostic information (mortality and morbidity, length of hospital stay, ICU stay time, duration of chest tube placement duration); and perioperative laboratory results, if applicable, including the levels of ALT, CR, CRP, Alb, Glu, and myocardial enzymes (baseline, 1 day presurgery, and 30 days postsurgery).

### Implementation timeline

The timeline of this study is 6 to 8 weeks; prehabilitation will be implemented for 2 to 4 weeks before surgery, and the follow-up period will include the 4 weeks after surgery. The timeline will differ across individuals, mainly due to the wait time before surgery. Clinical outcome data will be retrieved by practitioners from the inpatient records within 1 month after surgery. Figure 2 shows the full timeline.

**Fig. 2 Fig2:**
[figure not shown]
Timeline according to the SPIRIT guidelines. Time points: − 1, enrollment at thoracic outpatient clinic; 0, allocation; 1, waiting period before surgery; 2, day before surgery; and 3, 30 days after surgery. The pulmonary function test results will include the FEV1, FEV1%, FVC, FVC%, FEV1/FVC, PEF, and PEF% values; the qualitative questionnaires include the HADS, World Health Organization Disability Assessment Schedule II (WHODAS 2.0), and Postoperative Quality of Recovery-15 (QoR-15); the laboratory test results include the levels of ALT, CR, CRP, Alb, Glu, and myocardial enzymes; the clinical outcomes include the mortality and morbidity, length of hospital stay, ICU stay time, and duration of chest tube placement duration

### Sample size

In this study, we will calculate the sample size on the basis of a comparison of the measured primary outcome, the 6MWT result, between a small pilot study and a previous multimodal prehabilitation study conducted in our institute [15]. We will assume the average 6WMD in the aerobic prehabilitation group to be 30 m shorter than that in the multimodal group at 30 days postoperatively. The standard deviation (SD) for the 6MWD will be estimated to be 50 m for both groups. A sample size of 45 patients each in the aerobic group and multimodal prehabilitation group is required to detect a statistically significant difference at a two-sided significance level of 0.05 and statistical power of 90%. To account for patient dropout and missing data, we plan to recruit a total of 50 patients for each group.

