### Patient recruitment and allocation

In PUMCH, approximately 100–150 VATS lobectomy surgeries are scheduled each month. Patients will be recruited from the thoracic surgery outpatient department where they receive consults before surgery. When they are scheduled for VATS lobectomy, they will be screened for eligibility and asked to provide informed consent by a research staff. The patients included will then be randomly assigned to two equally sized groups, the multimodal prehabilitation group and the aerobic prehabilitation group, on the basis of a computer-generated sequence. The random allocation results will be concealed using sealed opaque envelopes. One of the main researchers of the study designs the statistical analysis plans and will be generating the allocation sequence. Two experienced anesthesiologist researchers will be in charge of enrolling and assigning participants according to the randomization result.

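### The sample size claims 90% power, but 45 patients per group gives 80% on the protocol's own inputs; 90% would need about 60 per group

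*Protocol article*

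**What the plan says.** All the inputs are in the Sample size section of the protocol article, apart from the allocation ratio:

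- **Difference:** mean 6MWD in the aerobic arm is taken to be "30 m shorter than that in the multimodal group at 30 days postoperatively".
- **Variability:** "The standard deviation (SD) for the 6MWD will be estimated to be 50 m for both groups".
- **Error rates:** the size given in the next point "is required to detect a statistically significant difference at a two-sided significance level of 0.05 and statistical power of 90" percent.
- **Size:** "A sample size of 45 patients each in the aerobic group and multimodal prehabilitation group" is given as the requirement. It is then raised to 50 per group for dropout and missing data, with no dropout rate stated.
- **Allocation:** patients are "randomly assigned to two equally sized groups" (Patient recruitment and allocation).

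The Statistical analysis section plans a linear mixed-effects model for 6MWD that examines the intervention-by-time interaction. It adjusts the primary outcome only if baseline imbalance is evident. Neither section gives a correlation between 6MWD measurements.

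**The concern.** A difference, a common SD, a two-sided alpha and equal allocation fully determine a two-sample comparison of means, so the claim can be checked directly. A standardised difference of 30/50 = 0.60 with 45 per group is the familiar configuration for 80% power, not 90%.

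At stake is how the trial is read. The comparator is an active programme, so a non-significant result is a realistic outcome. A reader told that the trial had 90% power would take such a result as stronger evidence against a 30 m benefit of the added components than the design supports.

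**Working it through.** **Inputs** (Sample size, and Patient recruitment and allocation): difference δ = 30 m; SD σ = 50 m in both arms; two-sided α = 0.05; 1:1 allocation; 45 evaluable and 50 recruited per group.

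**Step 1. Try to reproduce 45 per group at 90% power.** Normal approximation: n per group = 2(z₁₋α/₂ + z₁₋β)²(σ/δ)².

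- 90% power: 2 × (1.960 + 1.282)² × (50/30)² = 58.4, so 59 per group.
- 80% power: 2 × (1.960 + 0.842)² × (50/30)² = 43.6, so 44 per group.

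The noncentral t calculation gives:

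- 90% power: 59.35, so **60 per group**.
- 80% power: 44.59, so **45 per group**.

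The stated 45 is not reproduced at 90%. It is reproduced exactly by the t-test at 80%.

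**Step 2. Power at the stated sizes.**

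| Evaluable per group | t-test | Normal approximation |
|---|---|---|
| 45 | 80.4% | 81.2% |
| 50 (no losses at all) | 84.4% | 85.1% |

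The risk of missing a true 30 m difference is 100 − 80.4 = 19.6% at 45 per group and 100 − 84.4 = 15.6% at 50, against the implied 10%.

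**Step 3. What would make 90% true at 45 per group.** By the t-test, either a difference of 34.5 m with SD 50 m, or an SD of 43.4 m with a 30 m difference (34.2 m and 43.9 m by the normal approximation). The protocol states neither.

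**Step 4. Other readings of the sentence.**

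- *z instead of t:* changes n by one, not by 15.
- *One-sided α = 0.05:* power at 45 is 88.1% and 90% needs 49 per group; the text says two-sided in any case.
- *Dropout:* 45 is the figure before the allowance and 50 the figure after it, so the allowance does not explain the gap.

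**Step 5. Could use of the baseline value explain it?** The protocol gives no correlation r between baseline and day-30 6MWD, so the values below are assumptions. Two analyses are shown at 45 per group, with SD 50 m at both times:

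- baseline-adjusted (ANCOVA): effective SD = 50√(1 − r²);
- difference in change from baseline, one reading of the interaction at day 30: effective SD = 50√(2(1 − r)).

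| Assumed r | ANCOVA power | Change-from-baseline power |
|---|---|---|
| 0.3 | 83.9% | 66.2% |
| 0.4 | 86.7% | 72.9% |
| 0.5 | 90.2% | 80.4% |
| 0.62 | 94.8% | 89.8% |
| 0.63 | 95.2% | 90.5% |

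At r = 0.5 the ANCOVA SD is 50 × √0.75 = 43.3 m, which reaches 90%. The change-from-baseline SD is 50 × √1 = 50 m, which leaves power at 80.4%.

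**The case against.** The arithmetic is not seriously contestable. The best opposing case concerns what follows from it.

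- **The planned analysis is not a two-sample t-test.** It is a mixed model over repeated measurements, and its power may be above or below 80%. This is correct, and it means a corrected sentence should say that it refers to the day-30 comparison of means. It does not rescue the 90%, because the Sample size section describes a plain difference in means with a plain SD. The mixed model also helps or hurts depending on an unstated correlation.
- **The full protocol (version 2.1) is not shown and might contain a repeated-measures input.** This cannot be strictly excluded, but the exact match of 45 with the 80% t-test result makes it unlikely.
- **A miss risk of twice the stated one applies only if exactly 45 per group are evaluable.** This stands: with all 50 it is about 16%.
- **The protocol nowhere says that a null result would be read as equivalence.** This also stands. Over-reading is a risk, not something the plan commits to.
- **Reaching 90% through baseline adjustment is more than a wording change.** This stands too, because adjustment is at present conditional on imbalance.
- **Eighty percent is a conventional target and no patient is affected.** True, but the power stated for the primary outcome is still false.

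**Conclusion.** The stated power is wrong. On the protocol's own inputs, 45 per group gives 80.4% power (t-test) rather than 90%, an overstatement of about 10 percentage points. A 90% target would need 60 evaluable per group, 15 more per arm than stated. Full retention of the 50 recruited per group gives 84.4%.

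This rests on reading the section as what it describes: a two-sided comparison of two independent day-30 means with a common SD of 50 m. The likeliest explanation is that 80% was used in the calculation and 90% was written, but the document does not confirm this. The error does not invalidate the design; it misstates the design's sensitivity. It must be corrected.

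**What to change.** Replace the power sentence with wording such as:

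> For a two-sample comparison of mean 6MWD at day 30, with a true difference of 30 m, an SD of 50 m in each group and two-sided alpha 0.05, 45 evaluable patients per group give 80% power (84% if all 50 per group are evaluable).

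Carry the correction to any other place where the 90% figure is repeated. The cost is one sentence and a less favourable stated power. No patients are added and the analysis does not change. Recruitment was still open when the article appeared, and the Trial status section already commits the team to reporting important changes to the statistical plan.

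If the sponsor wishes to keep 90% without more patients, two further changes are needed. Baseline 6MWD must be adjusted for unconditionally in the primary analysis, and the assumed baseline to day-30 correlation must be stated with its source. With ANCOVA, r of at least 0.5 supports 90% at 45 per group. If the primary contrast is instead a difference in change from baseline, about 0.63 is needed. This route costs an amendment to the Statistical analysis section as well as to the sample size text.

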### Data collection

Upon receiving informed consent, the researchers will collect the patients’ medical history and demographic information at the baseline interview. Baseline laboratory test results will then be retrieved from patients’ electronic medical records: complete blood count (CBC), liver and kidney function test results, electrolyte levels, and coagulation routine test results.

The 6MWD and pulmonary function test will be conducted and recorded by trained researchers at our institution after they provide standardized instructions and demonstrations of the tests. Patient-reported qualitative questionnaires will be administered by and the results will be recorded by trained researchers.

During the prehabilitation period, message interviews will be sent to patients twice a week by our researchers, and feedback on weekly prehabilitation performance will be recorded.

After surgery, designated clinicians will retrieve the surgical approach performed, tumor assessment results, pathology results, and postoperative complications from the patients’ electronic records.

All the data will be collected by researchers who have signed a confidential disclosure agreement. Patients’ identity and personal information will not be disclosed without consent.

All data collected will be recorded first in the paper-based case report form (CRF) and then entered into a digital database by an independent investigator. The digital database will be under the supervision of the Data Monitoring Committee (DMC) composed of two experienced doctors from the Department of Anesthesiology and one statistician from the Department of Medical Research Center, PUMCH, who are independent from this study.

### Oversight and monitoring

The Project Manage Group consists of two main researchers who are experienced anesthesiologist researchers. They will meet with other team members every 2 weeks to oversee work in various phases, discussing problems met during recruitment and follow-up. All research investigators comprise the Trial Steering Committee, and they will meet every half year to supervise the research progress and discuss if there is a need to make amendments to the protocol. The Ethics Committee and sponsor hold auditing every year to review conduct.

The DMC members will monitor the integrity of the data and patient safety. Upon data entry, the database will be locked by a password. DMC members will make the decision to unblind, conduct an interim analysis, or terminate the trial, if they deem it necessary. The DMC members meet every month to discuss exercise injuries and other safety risks.

### Statistical analysis

Patients’ baseline characteristics will be described by descriptive analysis and compared between the groups to detect clinically relevant differences. If evident baseline imbalance exists, the analysis of the primary outcome will be adjusted. For tests conducted perioperatively including 6MWD, pulmonary function test results, HADS and WHODAS 2.0 score, a linear mixed-effects model will be built to analyze the interaction between intervention and time [18]. Other secondary outcomes including the QoR-15 score, length of hospital stay, chest tube duration, and postoperative complications will be analyzed using *χ*^2^ test and the Mann–Whitney *U* where appropriate. Patients lost to follow-up will be considered as non-adherence. We will perform sensitivity analysis to test if the analyses of the primary outcome will be robust to the missing values. All statistical analyses will be completed in R (R Foundation for Statistical Computing, Vienna, Austria; version 3.5.2).

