**Methods:**

This randomized pragmatic trial will be conducted in Peking Union Medical College Hospital (PUMCH) and include 100 patients who are eligible to undergo VATS lobectomy. Patients will be randomized to a multimodal or aerobic training group. Prehabilitation training guidance will be provided by a multidisciplinary care team. The patients in the multimodal group will perform aerobic exercises, resistance exercises, breathing exercises, psychological improvement strategies, and nutritional supplementation. Meanwhile, the patients in the aerobic group will conduct only aerobic exercises. The interventions will be home-based and supervised by medical providers. The patients will be followed up until 30 days after surgery to investigate whether the multimodal prehabilitation program differs from the aerobic training program in terms of the magnitude of improvement in functional capability pre- to postoperatively. The primary outcome will be the perioperative 6-min walk distance (6MWD). The secondary outcomes will include the postoperative pulmonary functional recovery status, health-related quality of life score, incidence of postoperative complications, and clinical outcomes.

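### The trial is sized on the 30-day difference in 6MWD, but the primary outcome is three unranked visits analysed by an intervention-by-time interaction, so the power statement does not describe the planned test

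*Protocol article*

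**What the plan says.** Four places in the protocol article bear on the primary comparison.

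- **Outcomes:** "The primary outcome will be the perioperative 6MWD", followed by three visits in parentheses: baseline, 1 day before surgery and 30 days after. No visit is singled out.
- **Sample size:** mean 6MWD in the aerobic group is assumed to be "30 m shorter than that in the multimodal group at 30 days postoperatively". The SD is given as follows: "The standard deviation (SD) for the 6MWD will be estimated to be 50 m for both groups". With two-sided 0.05 and 90% power this leads to 45 per group, raised to 50 for dropout and missing data.
- **Statistical analysis:** for 6MWD and the other repeatedly measured tests, "a linear mixed-effects model will be built to analyze the interaction between intervention and time". The coding of time is not stated, and no contrast from the model is named as primary.
- **Abstract, Methods:** the arms are to be compared "in terms of the magnitude of improvement in functional capability pre- to postoperatively".

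The research question in the Background speaks more generally of perioperative functional walking capacity.

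**The concern.** The calculation in Sample size concerns one number at one visit. The analysis in Statistical analysis concerns how the arms diverge over three visits. Nothing in the article links the two, so a reader cannot tell which result decides whether the trial succeeded.

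This has two consequences. First, the power quoted for the 30-day difference does not carry over to the interaction test. Second, an interaction test may respond to a difference on the day before surgery that has gone by day 30. Such a pattern is not far-fetched: under Implementation timeline, training takes place in the 2 to 4 weeks before surgery, so the day-before visit is where a training gain would be seen first. Without a named contrast, the result that is put forward as primary could also be chosen after the data are seen.

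**Working it through.** **Inputs from the article:** difference 30 m at day 30, SD 50 m, two-sided 0.05, 45 per group, visits at baseline, 1 day before surgery and day 30. **Assumed, because the article does not give them:** equal correlation r between any two visits (compound symmetry) of 0.3, 0.5 or 0.7, and the coding of time.

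**1. The sizing calculation.** The standard error of the day-30 difference is 50 × √(2/45) = 10.54 m, and 30/10.54 = 2.85. Power is Φ(2.85 − 1.96) ≈ 81%, whatever r is. The stated 90% would need n = 2 × (50/30)² × (1.960 + 1.282)² ≈ 58.4, so 59 per group. The stated 45 matches 80% power. That is a separate matter; what counts here is that this calculation describes a single-visit comparison.

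**2. Interaction with categorical time.** The joint test has 2 df: difference in change to the presurgery visit (d1) and difference in change to day 30 (d2). Under compound symmetry its noncentrality is

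λ = n(d1² + d2² − d1·d2) / [3 × SD² × (1 − r)].

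For d1 = 30, d2 = 0: λ = 45 × 900 / [7500(1 − r)] = 7.71, 10.8 and 18.0. For d1 = 15, d2 = 30: λ = 45 × 675 / [7500(1 − r)] = 5.79, 8.1 and 13.5. Referring λ to a noncentral chi-square with 2 df gives the probability of a positive test:

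| True difference (presurgery, day 30) | r = 0.3 | r = 0.5 | r = 0.7 |
|---|---|---|---|
| 30 m, 0 m | 70% | 85% | 97% |
| 30 m, 30 m | 70% | 85% | 97% |
| 15 m, 30 m | 57% | 72% | 92% |
| 20 m, 0 m | 36% | 49% | 72% |

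An F-test version gives nearly the same values (69%, 84% and 97% in the first row). The first two rows are identical because d1² + d2² − d1·d2 equals 900 in both. Under this structure the joint test is as likely to be positive for a benefit that has vanished by day 30 as for one that is sustained. In a simulation of the first row (5,000 trials), the interaction was significant without a significant day-30 contrast in 79% of trials at r = 0.5 and 92% at r = 0.7.

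**3. Interaction with linear time.** With visits coded −1, 0, 1, the presurgery visit has zero weight in the slope, so the 30 m then 0 m pattern is positive in about 5% of trials. With assumed visit days 0, 21 and 51 the figure is 6–7%. The equally spaced slope difference is half the difference in change from baseline to day 30. The standard error of that change is 50 × √(2(1 − r) × 2/45), so power for 30 m at day 30 is 67%, 81% and 96%. It agrees with the sizing figure only at r = 0.5.

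**4. The 30-day contrast, baseline-adjusted.** The standard error is 50 × √((1 − r²) × 2/45) = 10.06, 9.13 and 7.53 m. Power for 30 m is 85%, 91% and 98%, and the presurgery difference does not enter.

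**The case against.** The strongest reply is that coding of time and choice of contrast are details for an analysis plan that is not shown, and that the 70–97% figures depend on such a detail. The second half stands: the article does not say that time is categorical, and with linear time the effect all but disappears. The first half does not remove the point. The article itself states a sizing target, an outcome and an analysis, and these do not match as written.

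Several stronger readings are tempting, and the article does not support them.

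- *That the model gives no single effect estimate.* This is true only of the joint test. A mixed model with categorical time gives a group-by-day-30 coefficient with a confidence interval; what is absent is a statement that it is primary.
- *That type I error is inflated by testing each visit at 0.05.* Nowhere does the article say the visits will be tested separately.
- *That the abstract adds a conflicting third target.* If improvement is measured from baseline, the difference in change has the same expectation under randomisation as the 30-day difference. The abstract wording is loose rather than opposed.
- *That a presurgery-only benefit is a false positive.* The research question is perioperative capacity, and the presurgery visit is listed in the primary outcome. The 30 m then 0 m pattern is also extreme; at 20 m the figures are 36%, 49% and 72%.

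**Conclusion.** The mismatch is real and lies in what the article states: sizing on one visit, a primary outcome of three unranked visits, and an interaction as the only analysis. The stated power does not describe that analysis under either coding of time. With categorical time, 45 per group, SD 50 m and compound symmetry, a 30 m benefit confined to the day before surgery makes the joint test positive in about 70%, 85% and 97% of trials at assumed r = 0.3, 0.5 and 0.7. With linear, equally spaced time the figure is about 5%.

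A reader might infer that the trial is therefore underpowered. That does not follow. The interaction test may have more or less power than the sizing comparison's 81%: it has 57% for the 15 m then 30 m pattern at r = 0.3, and 97% for 30 m at both visits at r = 0.7. The fault is that the deciding comparison is not fixed, and it should be fixed before the data are analysed.

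**What to change.** Keep the mixed model and all three visits. State as the single primary test the multimodal-minus-aerobic difference in 6MWD at 30 days after surgery, the time point already used for sizing. Estimate it from that model with baseline 6MWD adjusted for, or constrained equal across arms, and test it at two-sided 0.05 with a 95% CI. Report the 1-day-presurgery contrast and the overall interaction as secondary, and state how time is coded. Bring the Abstract, Outcomes, Sample size and Statistical analysis sections into line with this.

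The cost is wording and a registry update, with no new data. The presurgery visit loses primary status, which the investigators must accept knowingly. Rewording does not by itself secure the stated 90% power: at 45 per group the adjusted contrast has 85% at r = 0.3 and reaches about 91% at r = 0.5. Sample size should therefore be restated for this contrast, with its assumed correlation.
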